# Clinical implementation of an algorithm for predicting exacerbations in patients with COPD in telemonitoring: a study protocol for a single-blinded randomized controlled trial

**DOI:** 10.1186/s13063-022-06292-y

**Published:** 2022-04-26

**Keywords:** Chronic obstructive pulmonary disease, Disease exacerbation, Physiological monitoring, Randomized controlled trial, Clinical decision support systems, Telemedicine, Forecasting, Machine learning, Health literacy

## Abstract

**Background:**

Acute exacerbations have a significant impact on patients with COPD by accelerating the decline in lung function leading to decreased health-related quality of life and survival time. In telehealth, health care professionals exercise clinical judgment over a physical distance. Telehealth has been implemented as a way to monitor patients more closely in daily life with an intention to intervene earlier when physical measurements indicate that health deteriorates. Several studies call for research investigating the ability of telehealth to automatically flag risk of exacerbations by applying the physical measurements that are collected as part of the monitoring routines to support health care professionals. However, more research is needed to further develop, test, and validate prediction algorithms to ensure that these algorithms improve outcomes before they are widely implemented in practice.

**Method:**

This trial tests a COPD prediction algorithm that is integrated into an existing telehealth system, which has been developed from the previous Danish large-scale trial, TeleCare North (NCT: 01984840). The COPD prediction algorithm aims to support clinical decisions by predicting the risk of exacerbations for patients with COPD based on selected physiological parameters. A prospective, parallel two-armed randomized controlled trial with approximately 200 participants with COPD will be conducted. The participants live in Aalborg municipality, which is located in the North Denmark Region. All participants are familiar with the telehealth system in advance. In addition to the participants’ usual weekly monitored measurements, they are asked to measure their oxygen saturation two more times a week during the trial period. The primary outcome is the number of exacerbations defined as an acute hospitalization from baseline to follow-up. Secondary outcomes include changes in health-related quality of life measured by both the 12-Item Short Form Survey version 2 and EuroQol-5 Dimension Questionnaire as well as the incremental cost-effectiveness ratio.

**Discussion:**

This trial seeks to explore whether the COPD prediction algorithm has the potential to support early detection of exacerbations in a telehealth setting. The COPD prediction algorithm may initiate timely treatment, which may decrease the number of hospitalizations.

**Trial registration:**

NCT05218525 (pending at clinicaltrials.gov) (date, month, year)

## Introduction

### Background

Chronic obstructive pulmonary disease (COPD) imposes a substantial economic and social burden globally [1, 2]. The global prevalence was estimated to 251 million cases in 2016 [3]. COPD is the third leading cause of morbidity and mortality worldwide [4] and is responsible for 3 million deaths annually [5]. The disease is projected to increase further over the coming decades with an estimated mortality of 4.5 million deaths annually by 2030 [6] and 5.4 million deaths annually by 2060 [2].

According to Global Initiative for Chronic Obstructive Lung Disease (GOLD) COPD refers to a group of progressive lung diseases characterized by not fully reversible airflow limitation that causes long-term breathing problems [2, 7]. In mild stages of COPD, the symptoms are present only by infections or by strenuous physical exertion. In the more severe stages of COPD, the symptoms are more prominent and will usually increase over time [8, 9]. Most patients with COPD experience periods where their symptoms vary from day to day [2]. However, sometimes patients also experience acute worsening of their usual symptoms, which are referred to as exacerbations. According to GOLD, an exacerbation is defined as “an acute worsening of respiratory symptoms that results in additional therapy” [7]. The frequency of exacerbations increases with the severity of COPD [10] and exacerbations contribute to the worsening of COPD at a long-term level [8, 11, 12]. Moreover, exacerbations are associated with increased mortality as well as impaired prognosis, decline in lung function, worsen cardiovascular comorbidities, and decreased health-related quality of life [8, 12, 13]. More than four out of five exacerbations can be managed outside the hospital with proper medication, whereas more severe exacerbations require ventilator support and hospitalization [7]. Early treatment is associated with faster recovery and decreased risk of emergency hospitalization [14]. However, patients with COPD often delay or fail to seek treatment during exacerbation [15], and it has been estimated that 40% to 70% of exacerbations remain unreported to healthcare personnel [14–16]. This highlights the importance of detecting exacerbations earlier in order to facilitate early and preventive treatment [14, 17].

### Rationale

Management strategies to prevent exacerbations include various pharmacological and non-pharmacological interventions [14, 18, 19]. However, the effect of these interventions remains moderate indicating the need for better management strategies [14, 18–21] that allow for earlier intervention while using scarce health care resources efficiently. Although telehealth interventions internationally show promising results related to admission rates and quality of life [15, 22–26], improvements in evidence are needed to come closer to identifying individual patients in risk of exacerbations in order to improve the outcomes of telehealth interventions [20, 21, 27]. In the TeleCare North trial, there were patients who benefitted greatly from having the telehealth system while others did not. Averaging this variability lead to the conclusion that patients experienced a non-statistically insignificant gain in health-related quality of life [28], increased sense of control, freedom, security, awareness of COPD symptoms [28–34] and that cost-effectiveness was most likely in the subgroup of patients with severe COPD [30]. In order to implement telehealth more effectively than by applying averaged results across clinical subgroups, machine-learning algorithms have been suggested as a way forward [35], e.g., by seeking to support clinical decisions in predicting exacerbations using patient physical measurements and other characteristics [27, 36–38].

Aalborg University has developed and optimized several COPD prediction algorithms for early detection of acute exacerbations that require hospitalization. These COPD prediction algorithms are based on both data from TeleCare North and a previous study conducted at the Department of Pulmonary Medicine at Aalborg University Hospital, Denmark [37–40]. The algorithms were based on mathematical features extracted from patients’ home measurements of pulse, blood pressure, and oxygen saturation. Since symptoms of an exacerbation are typically only present a few days prior to an exacerbation [10, 41] these algorithms underlined the importance of high-frequency measurements, to achieve the highest prediction accuracy [38, 41]. Experiences indicated that a frequency of at least 3 measurements each week, simple algorithms could achieve a sensitivity of 0.65 at a specificity of 0.95, whereas more advanced algorithms achieved a sensitivity up to 0.94 at a specificity of 0.95 [40]. It is therefore hypothesized that a prediction algorithm can reduce hospitalizations through facilitating an early and preventive treatment, which also can improve patients’ quality of life and lead to a greater economic effect of the telehealth intervention.

### Objective

In 2020, the Danish Government, Local Government Denmark, and Danish Regions initiated 15 signature projects to investigate, develop and test digital welfare solutions in the field of artificial intelligence [42]. This trial is established as one of these signature projects carried out on the initiative of Aalborg University, Aalborg Municipality, and the North Denmark Region. In this trial, the developed COPD algorithm from Aalborg University will be tested in an already implemented telehealth system. This algorithm is based on weekly measurements of blood pressure, pulse, and oxygen saturation from where the mean and variance are extracted. The COPD prediction algorithm aims to support clinical decisions by predicting exacerbations in patients with COPD based on physiological parameters. The trial is based on the hypothesis that by predicting exacerbations, the algorithm can reduce the number of acute hospitalizations and improve the health-related quality of life of patients with COPD and the cost-effectiveness of the telehealth solution. Hence, the primary objective of the study is to explore if the inclusion of an algorithm in a telehealth system can predict exacerbations and consequently reduce acute hospitalizations. The second objectives are to explore if inclusion of a prediction algorithm in a telehealth system leads to (1) improved health-related quality of life of patients with COPD and (2) improved cost-effectiveness of the telehealth solution.

## Methods

### Study setting

The TeleCare North trial was conducted between 2014 and 2015 [34] and its solution is currently operational in routine practice in the North Denmark Region. Patients with COPD are provided with an internet-based monitoring and treatment system, named Telekit [34]. The Telekit consists of a tablet (Galaxy TAB 2, 10.1, Samsung Electronics, Seoul, South Korea), a fingertip pulse oximeter (Nonin, Onyx II% SpO2, A and D Medical, Tokyo, Japan), a blood pressure monitor (Model UA-767, plus BT-C, Nonin Medical, MN, USA), and a scale (Precision Health Scale, UC-321PBT-C, A & D Medical, Tokyo, Japan) [43] (Fig. 1).

**Fig. 1 Fig1:**
[figure not shown]
The telehealth system, Telekit, consists of a tablet, a fingertip pulse oximeter, a blood pressure monitor, and a scale

The commercial and CE-marked telehealth system represents an open-source platform that collects health data and provides remote care for the patients with COPD. The telehealth system is based on a mobile- and web-based healthcare platform of which, the mobile platform is used by patients with COPD to measure their vital signs (blood pressure, oxygen saturation, pulse, and weight) and answer questions related to subjective parameters (such as shortness of breath, color of mucus) at home twice a week. The measurements and questions are then transferred wirelessly to specialized COPD community nurses. The specialized COPD community nurses use the web-based portal to monitor the patients’ health data on a weekly basis (measurements are typically reviewed Monday or Thursday) based on preset fixed alarms [43]. These preset fixed alarms are triggered by “too high” or “too low” single values of physiological parameters (oxygen saturation, pulse, blood pressure, and weight) that can be changed according to the individual needs. The specialized COPD community nurses are responsible for monitoring the patients’ vital signs and provide telephone advices over distance, if the vital signs deviate from the patients’ normal expected values. Such advice may lead the patient to adjust medication or to see a doctor.

### Study design

This trial is a prospective, parallel two-armed randomized (1:1) controlled trial with a nested full economic evaluation with 6 months follow-up. The trial is expected to run from October 2021 to May 2022. Prior to randomization, participants must give written consent in accordance with the Helsinki declaration [44]. Data will be anonymized and stored in accordance with the Danish Data Protection Rules [45]. The trial has been approved by the Regional Ethical Committee for Medical Research in the North Denmark Region (no.: N-20200076) and the Danish Data Protection Agency. Any protocol modifications will only be implemented after approval from the Regional Ethical Committee.

The trial is single-blinded, as the participants are unaware of their group allocation. The specialized COPD community nurses will not be blinded, as they will know whether the COPD prediction algorithm supports them or not. Outcome assessment will not be blinded.

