### Recruitment

The recruitment takes place in Aalborg Municipality. Specialized COPD community nurses identify eligible participants prior to randomization (Fig. 2). Subsequently, researchers will contact the participants to give them further information about the trial, answer potential questions, and guide them regarding the written consent form. A written consent form and questionnaires will be sent to eligible participants after receiving oral consent. If the participants still wish to participate in the trial, they will return the questionnaires and the written consent form via mail using a second pre-stamped envelope. The researchers’ telephone numbers are stated on the questionnaires giving the participants the opportunity to receive help in answering the questionnaires.

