### Randomization

The participants will, by a computer-generated list be allocated randomly (1:1) across two treatment arms: an intervention group (telehealth with algorithm) or to a control group (telehealth without the algorithm). The allocation sequence will be concealed until the participants are enrolled and assigned to the two groups. The randomization will not be performed until the included participants have signed informed consent and completed baseline questionnaires. Researchers at Aalborg University will generate the allocation sequence, enroll the participants, and assign the participants to their respective groups.

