## Intervention

All participants in both groups are encouraged to measure and transfer oxygen saturation, blood pressure, and pulse data three times per week. However, patients are also allowed to only measure and transmit oxygen and pulse data using the pulse oximeter if measuring blood pressure causes discomfort. Generally, the participants must measure their vital signs on fixed days in the week, starting either Monday or Thursday. Two monitoring schedules will occur depending on the participants measuring day. If the participants usually measure on Monday, they must perform additional measurements Wednesday and Friday. Whereas if the participants usually measure on Thursday, they must measure the additional measurements on Saturday and Monday. Thus, all specialized COPD community nurses will receive more data they can use in assessing the participants’ conditions during the trial period. The only difference between the two groups is that the specialized COPD community nurses monitoring the intervention group are aided by the COPD prediction algorithm, and the specialized COPD community nurses monitoring the control group are monitoring solely based on their professional opinion and the alarms implemented in the current telehealth system. The participants will be unaware of their group allocation. The specialized COPD community nurses will not be blinded. However, they are instructed not to tell the participants about their group allocation.

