Qualitative research interviews will also be conducted with selected participants and/or specialized COPD community nurses during and after trial completion, which will focus on data ethical aspects and user experiences of the telehealth system.

After trial completion, data is extracted comprising data from OpenTeleHealth (physical measurements) and relevant registers (all hospital contacts, all prescribed medicine, all contacts in primary sector, and all social sector contacts) in order to compare the number of exacerbations and the incremental-cost effectiveness ratio from baseline to 6 months follow-up between the intervention- and control group. All data will be stored in REDCap (Research Electronic Data Capture). Only researchers from Aalborg University will have access to the trial dataset.

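### Outcome assessment is declared unblinded without a reason, although only the nurses need to know the arm; masking is feasible at little cost

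*Protocol article*

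**What the plan says.** On blinding, the Study design section says: "The trial is single-blinded, as the participants are unaware of their group allocation". It then says that the nurses are not blinded, because they can see whether the algorithm supports them, and closes with "Outcome assessment will not be blinded". The Intervention section repeats that the nurses know the arm and adds: "However, they are instructed not to tell the participants about their group allocation".

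On roles, the Rationale says that "Aalborg University has developed and optimized several COPD prediction algorithms", and the Objective confirms that "the developed COPD algorithm from Aalborg University will be tested in an already implemented telehealth system". Under Randomization: "Researchers at Aalborg University will generate the allocation sequence, enroll the participants, and assign the participants to their respective groups". Under Explorative outcomes, and again under Data Availability: "Only researchers from Aalborg University will have access to the trial dataset".

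On data collection:
- The primary outcome is the number of all-cause acute admissions over the six months. It is obtained from registers covering all hospital contacts, extracted once the trial is over.
- SF-12v2 and EQ-5D-5L are posted to participants at baseline and at six months.
- If a participant cannot post the forms back, someone from the research team fetches them from the home. The section on minimal loss to follow-up calls this person a researcher; Explorative outcomes says a research assistant.

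**The concern.** The lack of blinding is a stated rule, not a silence that an analysis plan might fill. The article gives a reason for unblinding the nurses, since their use of the alarm is the intervention. It gives none for the people who derive or collect outcomes.

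Two routes by which knowledge of the arm could matter remain open:
- **Register data.** An extract of hospital contacts has to be turned into a count of acute admissions, and other register entries into resource use. This leaves some room for choices, for example on what counts as acute or how transfers are handled, and it concerns the primary endpoint.
- **Quality-of-life forms.** The forms are subjective. Participant blinding is the only blinding in the trial. The nurses are told not to reveal the arm; the article states no matching instruction for research staff who may know it and may come to the home.

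The institution has an interest in its own algorithm, so a result in the algorithm's favour would be easier to defend if these steps had been masked.

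**Working it through.** The document gives no figure for this point and no arithmetic applies. Masking changes neither the sample size nor the power nor the significance level. The check is to set each task beside what the article says and ask whether the arm must be known.

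1. **Nurse monitoring (Intervention; Intervention group).** The nurses of the intervention group see the prediction alarm. The arm must be known.

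2. **Baseline questionnaires (Recruitment; Randomization).** They are returned with the consent form, and randomization waits until both are in. No allocation exists yet, so it cannot influence the answers.

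3. **Six-month questionnaires (Explorative outcomes, Table 1; Measures to ensure minimal loss to follow up).** They go by post to participants who do not know their arm. The only research-team contact stated for their return is fetching the envelope. Fetching does not require the arm to be known.

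4. **Admissions (Primary outcome; Explorative outcomes).** The endpoint is all-cause, so nobody has to judge whether an admission was due to COPD. The source is a register extract made after the trial ends. Turning contacts into a count does not require the arm to be known, and the timing makes a file without the arm variable practicable.

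5. **Costs (Statistical methods).** Hospital, medication, primary care and municipal resource use can be derived without the arm. The cost of implementing the algorithm arises in the intervention arm only. Total cost therefore cannot be completed until the allocation is merged; the underlying resource use can.

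6. **Questionnaire scores (Statistical methods).** Scoring SF-12v2 and EQ-5D-5L does not require the arm to be known.

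Of the tasks after randomization, only the nurses' monitoring and the last step of the cost calculation need the allocation. The blanket statement that assessment is unblinded therefore covers several steps that could be masked.

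**Who could know the arm.** The Rationale and Objective place development of the algorithm at Aalborg University, Randomization places sequence generation and assignment there, and Explorative outcomes restricts data access to its researchers. The overlap is of institution. Overlap of persons is neither shown nor excluded.

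**The case against.** The strongest reply is that little is left to bias. An all-cause register count leaves an assessor small discretion. The quality-of-life answers come from blinded participants on postal forms, and fetching an envelope is not assessment. The unblinded nurses, whose calls can influence whether a patient is admitted, are probably a larger source of bias, and masking the assessors does nothing about it. All of this stands and limits the weight of the point. It does not supply a reason for leaving the other steps unmasked.

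Some stronger readings are tempting but not supported:
- **Unblinded researchers help patients answer the follow-up forms.** The Recruitment section says that the researchers' "telephone numbers are stated on the questionnaires giving the participants the opportunity to receive help in answering the questionnaires". That passage concerns forms completed before randomization. The same help at six months is plausible, because telephone numbers may be printed on those forms too, but it is not stated.
- **The developers themselves randomize, collect and code.** The article names the university and its researchers, not individuals or one group.
- **Researchers who know the arm decide case by case which contacts count.** No such step is described.
- **Allocation concealment is compromised.** The article states a computer-generated list, concealment until enrolment and assignment, and randomization only after consent and baseline forms. Who loads the list and who can see it is detail that an article may leave to the full protocol.

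**Conclusion.** The point holds in a limited form. The protocol fixes unblinded outcome assessment without a reason, at an institution that developed the algorithm, controls the allocation and alone has access to the data. Several of the steps concerned do not need the arm.

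The likely bias is small, for the reasons conceded above, and the document offers no basis for computing it. Any figure would rest on assumed rates of help or misclassification, so none is given.

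The conclusion assumes that the sentence in Study design means what it says for all outcomes, and that the register extract can be prepared without the arm variable. The article says nothing against the latter. A reader might infer that masking is free; the article does not support that, because the same institution enrols, assigns and analyses, and would have to divide those tasks. What can be said is that an avoidable source of bias can be removed at little cost, so the sentence should be changed.

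**What to change.** Replace the sentence in Study design by a rule with two parts:

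- Counts of acute hospitalizations, register resource use and questionnaire scores are derived from a file that does not contain the arm variable. The allocation, together with the algorithm cost that applies to one arm only, is merged after that dataset is locked.
- Staff who collect the 6-month questionnaires, or who are asked for help with them, have no access to the allocation field in REDCap.

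The cost lies in setting access rights in a database already in use and in the order of the data-management steps. No visit, measurement or sample size changes. The downside is that the team must keep these tasks and access rights apart. The change does not address any effect of the nurses' knowledge of the arm, which is inherent in the intervention.
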